## Abstract

Vascular endothelium insults caused by high serum glucose levels affect the oxygen supply to tissues, via the microvascular endothelium, resulting in an increased perfusion heterogeneity. These insults may lead to the underuse of blood capillaries, while other vessels are overused and effectively overload their oxygen supply capacity, which eventually causes damages to distal parts of the peripheral nervous system. Therefore, the proprioceptive and exteroceptive feedback information will be gradually lost and contribute to a mobility reduction. This study aims to assess the efficacy of whole-body vibration (WBV) associated with strength training (ST) on lower-limb blood flow and mobility in older adults with type 2 diabetes (DM2). Methods and analyses: This is a protocol (1st version) for Pa single-blind, randomized, controlled clinical trial guided by the SPIRIT guidelines. Our sample will consist of 51 older adults with DM2 randomly allocated to three groups: low frequency WBV (16–26 Hz) associated to ST (G1), WBV sham (G2) and nonintervention control (G3). The study protocol is set for a 12-week (three times per week) schedule. Primary outcomes: skin temperature using infrared thermographic imaging (ITI); mean peripheral arterial blood flow velocity (MBF) by a handheld Doppler ultrasound (DU), and functional mobility by Timed Up and Go (TUG) test. Secondary outcomes: quasi-static posture using the DX100 BTS Smart optoelectronic system, and plantar pressure and body balance using the MPS stabilometric platform. Data will be collected and analyzed at baseline and post-intervention, considering *p*-value < 0.05 level of significance. The analyses will also be conducted with an intention-to-treat method and effect size. Dissemination: All results will be published in peer-reviewed journals as well as presented in conferences.

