### 2.7. Outcome Measurements

#### 2.7.1. Primary Outcomes

**Skin temperature**

The thermographic imaging of lower limbs will be captured by FLIR E40bx^®^ camera (FLIR^®^ Company, Wilsonville, Oregon, EUA), with thermal sensibility of 0.5 °C, light emission value of 0.987 and 160 × 120 pixels resolution. The camera will be positioned at a distance of 1 m from the regions of interest with a 90° angle (perpendicular) relative to the camera lens [49].

The volunteers will have fifteen minutes for acclimatization and rest as the body temperature comes into alignment with the room temperature. The test room temperature will be controlled at 18 °C and 23 °C with relative air humidity between 40 and 70% monitored with a precise thermo hygrometer (KT-908). All volunteers will be previously oriented to avoid pain killers or vasoactive drugs, lotions or moisturizing creams on the regions of interest, in addition to caffeine and nicotine in the 4 h before the exam [49].

After the acclimatization period, the thermal images of the interest points will be registered and, subsequently, the mean temperature will be analyzed by the thermographic software provided by the manufacturer (FLIR^®^ Tools). Table 3 shows the six regions of interest [50]. All the photographic images will be collected by one evaluator only with expertise in managing the camera.

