### 2.9. Data Processing and Analysis

All data records will be kept under custody of LACIRTEM lab and an allocation-blind statistician will conduct all analysis using Statistical Package for the Social Science (SPSS, IBM^®^, EUA), version 23.0, with 5% (*p* < 0.05) level of significance.

Sociodemographic, anthropometric and baseline clinical data for both groups will be expressed as the mean and standard deviation for continuous variables, proportions and percentages for nominal variables. The Kruskal–Wallis H test will be used for continuous variables and Chi-square test will be used to associate nominal variables in order to verify homogeneity between baseline data among the groups. 

All analysis will be conducted in accordance with the intention-to-treat method (ITT) using the last observation carried forward (LOCF) method, which inputs baseline data at postintervention for the dropout cases [59]. Missing values due to participants’ nonattendance or withdrawal are expected in clinical trials. Continuous variables with normal distribution will be expressed as mean and standard deviation and the intra-group comparison will be performed by paired *t*-test, and the inter-group comparison by analysis of variance (ANOVA). For nonnormal continuous variables, data will be expressed in median and interquartile intervals (Q25–Q75) and compared within the groups by Wilcoxon test and among the groups by Kruskal–Wallis H test. Size effect will be calculated to support the statistical significance. 

We will also investigate and register the possible adverse events during the treatment protocol. 

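### The between-group ANOVA is unadjusted and its response is not stated, so precision available from the measured baseline values is lost; ANCOVA on baseline recovers it

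*Protocol article*

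**What the plan says.** The Abstract commits to measuring at two time points: "Data will be collected and analyzed at baseline and post-intervention". Section 2.9 then fixes the methods.

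- Normal outcomes: "the intra-group comparison will be performed by paired *t*-test" and, between arms, "and the inter-group comparison by analysis of variance (ANOVA").
- Non-normal outcomes: Wilcoxon within arms, and a comparison "among the groups by Kruskal–Wallis H test".
- Baseline data: compared across arms by Kruskal–Wallis or chi-square tests "in order to verify homogeneity between baseline data among the groups". No action follows from the result.
- Dropouts: last observation carried forward, "which inputs baseline data at postintervention for the dropout cases".

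No covariate is named for any between-group test. Nor does the section say whether ANOVA is applied to post values or to changes from baseline.

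For thermography, the Skin temperature part of section 2.7.1 says "The test room temperature will be controlled at" 18 and 23 °C, with "relative air humidity between 40 and 70% monitored with a precise thermo hygrometer". It does not say that a room temperature is logged for each examination.

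**The concern.** Baseline values have three stated uses: paired tests inside each arm, homogeneity tests and filling in dropouts. None of these improves the randomised comparison. With 17 per arm, the arms can differ appreciably at baseline by chance, and an unadjusted comparison of post values carries part of that difference into the estimate as noise. A homogeneity test does not remove it.

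The hypothesis in the Introduction is that adding vibration to strength training enhances the benefit, which is the G1–G2 contrast. Separate paired tests do not estimate that contrast. If one arm reaches significance and another does not, that is not evidence that the arms differ, yet placing the two sets of tests side by side makes such a reading easy.

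The unstated response is a second gap. Post-value and change-score ANOVA have different precision and can give different answers in the same data, so the choice should not remain open until the data are seen.

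**Working it through.** **Inputs.** From section 2.4: 17 enrolled per arm, 80% power, two-sided 5%, about 20% dropout. From section 2.9: the tests above. Assumed, because the document gives no value: a baseline-to-post correlation ρ of 0.3 to 0.8, equal SDs at the two visits and, for the power figures, a true difference of 0.8 SD.

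**The plan's own figure.** Section 2.4 states about 15 per arm from 40% against 10%. With P(1 − P) taken as the mean of the two arm variances, (0.24 + 0.09)/2 = 0.165, the printed formula gives 7.849 × 0.165 / 0.30² = 14.4, so 15. That calculation compares proportions. It gives no planned precision for a continuous outcome, so the check below starts from the 17 per arm.

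**Variance of a pairwise difference, relative to post-value ANOVA.**

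- Post-value ANOVA: 1
- Change-score ANOVA: 2(1 − ρ)
- ANCOVA on baseline: 1 − ρ²
- ANCOVA relative to change-score ANOVA: (1 − ρ²) / [2(1 − ρ)] = (1 + ρ)/2

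Both ANCOVA ratios are below 1 for every ρ between 0 and 1.

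**Results at 17 per arm.** Power is from the noncentral t with 3 × 17 − 3 = 48 degrees of freedom (47 for ANCOVA). Post-value ANOVA detects (2.011 + 0.849) × √(2/17) = 0.98 SD with 80% power, and has 63% power at 0.8 SD.

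| ρ | ANCOVA ÷ post-value | Change ÷ post-value | ANCOVA ÷ change | Detectable with ANCOVA (SD) | Equivalent n per arm, 17/(1 − ρ²) | Power at 0.8 SD: change / ANCOVA |
|---|---|---|---|---|---|---|
| 0.3 | 0.91 | 1.40 | 0.65 | 0.94 | 18.7 | 49% / 67% |
| 0.5 | 0.75 | 1.00 | 0.75 | 0.85 | 22.7 | 63% / 75% |
| 0.6 | 0.64 | 0.80 | 0.80 | 0.79 | 26.6 | 72% / 82% |
| 0.7 | 0.51 | 0.60 | 0.85 | 0.70 | 33.3 | 84% / 89% |
| 0.8 | 0.36 | 0.40 | 0.90 | 0.59 | 47.2 | 95% / 97% |

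The equivalent n is relative to post-value ANOVA. Simulation at ρ = 0.6 and 0.8 SD gave 64%, 73% and 81% power for post-value, change-score and ANCOVA, in agreement with the table.

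**Chance imbalance.** The baseline difference between two arms of 17 has standard deviation √(2/17) = 0.34 SD. A difference beyond 0.5 SD therefore occurs about 15% of the time for each pair of arms and each outcome. On average, a post-value comparison carries ρ times that difference.

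**Within-group tests.** Suppose two arms have the same true change of 0.5 SD, with ρ = 0.6 and 17 per arm. Each paired test has power 0.581. The chance that exactly one arm is significant is 2 × 0.581 × 0.419 = 0.49, although the arms do not differ. For true changes of 0.3 and 0.7 SD this chance is 0.38 and 0.25.

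**Dropouts.** At 20% dropout about 17 × 0.8 = 13.6, so 14, per arm have an observed post value. At 14 per arm the detectable difference is 1.09 SD for post-value ANOVA and 1.04 to 0.65 SD for ANCOVA over the same ρ. For the rest, post equals baseline by construction. This raises the correlation in the imputed data, and precision gained that way is not information.

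**The case against.** The strongest reply is that this concerns efficiency, not validity. Under randomisation an unadjusted ANOVA is unbiased and its standard error already allows for chance imbalance. Section 2.9 does specify a between-group test, so misuse of the paired tests is a risk and not part of the plan. This stands, and it limits the weight of the point. The size of the gain also rests on a correlation that the document does not give: at ρ = 0.3 the standard error falls by only 4.6% against post-value ANOVA.

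A reader might infer more than the document supports in two respects.

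- **That baseline is ignored altogether.** This would be so only if the ANOVA response is the post value. If changes are analysed, baseline enters, though inefficiently, and at ρ = 0.8 the detectable difference moves only from 0.98 × √0.40 = 0.62 SD to 0.59 SD. The text does not settle which is meant.
- **That room temperature is a recorded covariate waiting to be used, and that its 5 °C band swamps the 0.5 °C called important.** The document describes control and monitoring of the room, not a logged value per examination. The 0.5 °C in section 2.4 is an asymmetry at the anterior knee, and a shared room temperature would largely cancel in a side-to-side difference. The mean regional temperatures in section 2.7.1 would not have that protection, but the document gives no figure for how far skin temperature follows room temperature. No magnitude can be claimed.

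The point cannot be set aside as detail left to an analysis plan, because the article itself names the tests.

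**Conclusion.** The concern holds in a limited form. The planned between-group test is valid but less precise than the data allow, and its response variable is undefined. Against post-value ANOVA, baseline adjustment cuts variance by 9% to 64% and lowers the detectable difference from 0.98 SD to between 0.94 and 0.59 SD. Against change-score ANOVA the cut runs from 35% down to 10%. These figures assume ρ between 0.3 and 0.8, equal SDs at both visits and 17 informative participants per arm; with dropout the true gain is smaller than imputed data would suggest. The direction does not depend on the exact correlation, since ANCOVA has the lower variance under either reading for any ρ between 0 and 1. The change should be made, but the current plan is not invalid without it.

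**What to change.** In section 2.9, for each continuous outcome, make the primary between-group analysis an ANCOVA of the post-intervention value on arm (three levels) plus the baseline value of that outcome. Report adjusted G1–G2 and G1–G3 differences with 95% confidence intervals. This also settles the unstated response. Label the paired t and Wilcoxon tests as descriptive and drop the baseline homogeneity p-values, keeping the descriptive baseline table. When reporting precision, note that carrying baseline forward for dropouts inflates the apparent correlation.

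Room temperature is at most a secondary covariate, for mean regional skin temperature only, and only if the monitored value is logged at each examination.

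The baseline adjustment changes analysis wording only: the baseline values are already planned, the model runs in the SPSS version named, and no participants or outcome measurements are added. Logging room temperature, if wanted, would be one extra entry per thermography examination.

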## 2. Materials and Methods

This randomized clinical trial was approved by ethics committee of the research institution, Universidade Federal de Pernambuco, under No. 2.449.800, and it complies with the ethical aspects based on Resolution 466/12 of the National Health Council and the Declaration of Helsinki. 

All volunteers will provide written consent after being informed of the study procedures, possible risks and their right to withdraw at any time, with no consequences for any further treatment. The confidentiality of volunteer data will be protected.

According to the recommendations of the CONSORT extension, possible damages will be reported, resulting in the immediate interruption of treatment [33]. The volunteer will be referred to the emergency department of the research institution hospital if a serious adverse event to the treatment is identified, such as functional disability and/or a life threatening outcome.

The dataset will be stored in a locked room in the LACIRTEM lab in password-protected computer files. These data will be disseminated after completion of the study in international peer-reviewed scientific journals and presented at conferences. Positive, negative and inconclusive results will be published in peer-reviewed journals and presented at national and international conferences. In addition, the data will be shared with the volunteers.

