### 2.1. Experimental Design and Location

This is a 12-week (3 times a week), single-blind, randomized, controlled clinical trial with three arms (low-frequency WBV associated with ST, G1; WBV sham associated with ST, G1; and control, G3). The study will be developed in the Kinesiotherapy and Manual therapy Laboratory (LACIRTEM) of the Department of Physiotherapy in the Universidade Federal de Pernambuco (UFPE). Figure 1 is a detailed flow chart of the volunteers.

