### 2.3. Eligibility Criteria

Inclusion: Men and women between 60 and 80 years old with 2 years of clinical diagnosis of DM2 and pre-obesity (25.0–29.9 kg/m^2^) or with obesity class I (30.0–34.9 kg/m^2^) [34], functionally independent, with no severe foot deformity that may require special footwear, other orthopedic deformities, no high risk of falls, no balance disorders, deep venous thrombosis or need for assistive devices for ambulation, preserved cognitive function assessed by Mini-Mental State Examination (MMSE), considering 19 as cutoff point for poor cognitive function [35], and sedentary (0 to 5 points) or poorly engaged in physical active (6 to 11 points) accordingly to the questionnaire of Habitual Physical Activity (HPA) [36].

Exclusion: Change in the subject’s current medication during the study, secondary physical activity during the training program and persistent hypertensive crisis (≥180 × 110 mmHg) or elevated capillary blood glucose (≥300 mg/dL) that prevent the training program completion.

No compliance: Attendance rate lower than 75% of the scheduled sessions, corresponding to 27 sessions. 

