On the platform, barefoot volunteers will adopt an isometric squat positioning at 40°, verified with a conventional goniometer. On their heels, silicon insole will be applied (semi-rigid) in order to keep only the forefoot and middle-foot in direct contact with the platform surface, thus correcting the body weight distribution and foot biomechanics changes. Both strategies will be used to minimize the axial transmission to cranial base [7,21,47]. In accordance with the International Organization for Standardization (ISO) 2631-1, all the parameters are considered safe for body exposure to mechanical vibration [48].

The WBV sham (simulation) will be performed with the platform unplugged. A speaker connected to the platform will emit a similar sound during the time equivalent to the protocol, since the vibrating stimulus cannot be visually differentiated. The volunteers that experience the simulation will have to adopt the same squat positioning during the session. We will assure no contact between volunteers from arms G1 and G2 [47].

The volunteers in arm G3 group will be instructed to manage their diabetes as usual routine without practicing physical activity. All of them will be informed that they will be scheduled to receive the treatment after 12 weeks. 

It is worth mentioning that the entire intervention team will be submitted to a complete 8 h training. 

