### 2.8. Monitoring Measurements

**Vital signs and capillary glycemia**

Before and right after each session, systolic (SBP) and diastolic (DBP) blood pressure will be measured by an aneroid sphygmomanometer and a stethoscope (Premium, China), and will be classified according to the recommendations from the Brazilian Society of Cardiology [56].

The number of breaths per minute (RR) will be registered by the chest movement or abdominal compartment for a 60 s period, and the heart rate (FR) and peripheral oxygen saturation (SpO2) will be measured by a portable pulse oximeter (More Fitness, MF-416, China) [57]. 

Capillary glycemia will be monitored by a portable blood glucose meter (ACCU-CHEK^®^ Active, Roche Diabetes Care, model GU) in accordance with the parameters recommended by ISO 15197:2013 [58].

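### Blood pressure checks are tied to training sessions and adverse event recording to the treatment protocol, with nothing equivalent described for untreated G3, so a by-arm harms report that includes G3 is open to detection bias.

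*Protocol article*

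**What the plan says.** Four places in the protocol article bear on this.

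- **Section 2.9 (Data Processing and Analysis)** closes with the only sentence on recording adverse events: "We will also investigate and register the possible adverse events during the treatment protocol". It names no arm, method or frequency.
- **Section 2.8 (Monitoring Measurements)** fixes the timing of blood pressure: "Before and right after each session, systolic (SBP) and diastolic (DBP) blood pressure will be measured". Glucose follows under the same heading: "Capillary glycemia will be monitored by a portable blood glucose meter", with no timing of its own.
- **Section 2 (Materials and Methods)** refers to the CONSORT extension and says that "possible damages will be reported, resulting in the immediate interruption of treatment". A volunteer is sent to the emergency department "if a serious adverse event to the treatment is identified, such as functional disability and/or a life threatening outcome".
- **Section 2.6 (Intervention)** describes the untreated arm: "The volunteers in arm G3 group will be instructed to manage their diabetes as usual routine without practicing physical activity". G3 is offered treatment only once the 12 weeks are over.

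By contrast, the part of section 2.8 on other biochemical markers places HbA1c and lipids at the initial assessment and the 12-week reassessment, without limiting them to any arm.

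**The concern.** Each statement about harms is anchored to treatment, and the blood pressure schedule to sessions. During the comparison period G3 has neither. Staff would see G1 and G2 volunteers several times a week and take readings each time. For G3 the article describes no contact between baseline and week 12 and no adverse event question at week 12.

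Raised blood pressure, high glucose and intercurrent illness also occur in older adults with type 2 diabetes who do not train. If one arm is watched closely and another is not, background events are written down in the first and missed in the second.

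What is at stake is the use of G3 as the reference for harms. G1 versus G2 isolates vibration. Only G3 can show whether events under the whole programme exceed what would have happened anyway. A harms table with three columns invites that reading even if no test is attached.

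**Working it through.** **Inputs from the protocol article**

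- Schedule: "This is a 12-week (3 times a week), single-blind, randomized, controlled clinical trial with three arms" (section 2.1). Section 2.6 gives the strength programme equally to G1 and G2.
- Attendance threshold: "Attendance rate lower than 75% of the scheduled sessions, corresponding to 27 sessions" (section 2.3).
- Blood pressure: two measurements per session (section 2.8).
- Planned size: 17 per arm (section 2.4).

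**Reproducing the plan's own figure**

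Sessions = 12 weeks × 3 = 36. Threshold = 0.75 × 36 = 27. This agrees with section 2.3, so 36 is the right count of planned contacts.

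**Planned ascertainment per volunteer over the 12 weeks**

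| | G1 or G2, full attendance | G1 or G2, 27 sessions | G3 |
|---|---|---|---|
| Session contacts | 36 | 27 | none described |
| Blood pressure readings | 36 × 2 = 72 | 27 × 2 = 54 | none described |

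G1 and G2 have identical columns, so the imbalance concerns only comparisons with G3.

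**Can the size be worked out?**

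No. It depends on the true event risk and on the share of events that would come to light in G3, and the document gives neither. The following is assumption only. Let the true risk r be the same in every arm, let all events be detected in G1, and let a fraction d be detected in G3. Expected volunteers with a recorded event are 17 × r in G1 and 17 × r × d in G3.

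| Assumed r | G1 | G3, d = 0 | G3, d = 0.5 | G3, d = 1 |
|---|---|---|---|---|
| 10% | 1.7 | 0 | 0.85 | 1.7 |
| 30% | 5.1 | 0 | 2.55 | 5.1 |

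With no true difference, the apparent excess in G1 runs from 0 (d = 1) to 5.1 volunteers of 17 (r = 30%, d = 0). The direction is fixed, in that G3 looks safer. The size is not.

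**The case against.** The strongest reply is that section 2.9 does not exclude G3. The training protocol lasts 12 weeks, so the phrase can be read as the trial period in every arm. The source is also a condensed article, and adverse event forms and contact schedules commonly stand in the full protocol. Both points are fair. A reader might infer that G3 has no harm ascertainment at all, or that no event in G3 could satisfy the wording. The text does not say so, and G3 is not excluded from the 12-week reassessment, where events could be asked about. What remains is that the one stated schedule, for blood pressure, is session-bound, and the one adverse event sentence leans towards treatment.

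Three other stronger readings also fail.

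- **Serious events must be attributed to treatment before they count.** The wording in section 2 that suggests this belongs to an emergency referral rule. It does not define what is recorded.
- **The chance of at least one limit crossing in 72 readings measures the bias.** The blood pressure and glucose limits in section 2.3 are exclusion criteria, tied to a persistent crisis or elevated glucose that stops a volunteer finishing the programme. A single high reading is not that event. Repeated readings in one person are also correlated, and the document gives no risk per reading.
- **The trial's harms results are biased.** No between-arm comparison of harms is specified, and the hypothesis, vibration added to strength training, concerns G1 versus G2, which this does not touch.

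It is also true that over-detection in G1 and G2 would make training look less safe, so it could not by itself produce a false claim of safety. It would still leave a real excess over G3 indistinguishable from an artefact.

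**Conclusion.** The point stands as a specific, inexpensive improvement. It does not show a flaw in any planned test. As written, ascertainment during follow-up is unequal: up to 36 session contacts and 72 blood pressure readings per G1 or G2 volunteer (54 at 27 sessions), against none described in G3. If harms are reported by arm, an excess in G1 or G2 over G3 could reflect detection alone.

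This rests on two conditions: that the article's wording is followed as it stands, and that G3 appears in the harms report. If the full protocol already sets equal questions in all arms, only the published sentence needs correcting.

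**What to change.** **In section 2.9**

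- State that all adverse events are registered from randomisation to the week-12 reassessment in all three arms, whether or not they are judged related to treatment.
- Use the same questions at the same times in every arm. The minimum is a short list put by the blinded assessor at the week-12 visit. Asking it after the outcome measurements keeps the answers from revealing the allocation before those are taken.
- Optionally, call G3 at two interim times, for example weeks 4 and 8, and put the same questions to G1 and G2 in those weeks.
- Compare session-detected blood pressure or glucose events between G1 and G2 only. Base any comparison with G3 on identically collected data.

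**Cost**

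The minimum needs a change of wording and a few minutes at a visit that already takes place. The optional calls come to 17 × 2 = 34. The downside is a little staff time and slight extra contact with G3. Volunteers still know whether they are training (section 2.5), so equal questions remove the difference in opportunity to report but not every difference in readiness to report.
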